## Abstract

**Background:**

Hepatitis B virus (HBV) and hepatitis C virus (HCV) are significant global health concerns, particularly prevalent in low- and middle-income countries (LMICs). In China, a significant number of international migrants from LMICs reside, many of whom are at high risk of HBV and HCV infection, while this group tends to engage in low HBV and HCV test use due to some adverse factors. Pay-it-forward (PIF) is a social innovation strategy that is based on the theories of upstream reciprocity and mutual aid. Previous studies have shown that the PIF strategy has proven effective in promoting sexually transmitted infections (STIs) testing in various populations.

**Objective:**

This study aims to evaluate the effectiveness of a PIF intervention in promoting HBV and HCV testing among international migrants from LMICs in China.

**Methods:**

A 2-arm cluster randomized controlled trial (RCT) will be conducted in Guangzhou, China. Participants will be recruited from a public hospital serving a large migrant community. A total of 100 eligible participants will be enrolled in blocks of 5 using a cluster randomization plan and randomly assigned to either the PIF intervention arm or the control arm in a 1:1 ratio. Participants in the intervention arm will watch a 2-minute video introducing the PIF concept and receive printed educational materials on HBV and HCV. Participants will then be offered free testing donated by previous participants, which they can accept or decline, and an opportunity to make a monetary donation to cover testing for a future participant. Control arm participants will receive standard medical services, with self-paid testing. The primary outcome is the proportion of participants tested for both HBV and HCV. Data will be collected through a self-administered questionnaire, and test information will be obtained from the hospital’s medical records without personally identifiable information. The survey data will be analyzed using generalized estimating equations to account for clustering effects.

**Results:**

This protocol was completed in August 2024, and implementation was conducted from September 2024 to February 2025. According to the baseline survey findings, 73.0% (73/100) of the 100 eligible participants recruited were male, 87.0% (87/100) were from African countries, and 85.0% (85/100) came to China for business purposes. About 40.0% (40/100) earned more than US $1100 per month, 62.0% (62/100) were married, and 6% (6/100) had both stable and casual sexual partners.

**Conclusions:**

This study is innovative in targeting international migrants from LMICs in China and using the PIF strategy to promote HBV and HCV testing. The PIF intervention is expected to increase testing rates by addressing financial barriers and fostering community support. The findings will contribute to the understanding of HBV and HCV testing promotion among this understudied population, with potential implications for public health policy and practice.

## Introduction

Hepatitis B virus (HBV) and hepatitis C virus (HCV) are both causes of acute and chronic disease and can be transmitted through unprotected sexual intercourse, infected blood, and mother-to-child transmission during pregnancy. Globally, the World Health Organization (WHO) estimates 254 million people have an HBV infection and 50 million people have an HCV infection, respectively [1,2]. Low- and middle-income countries (LMICs) experience a severe hepatitis burden, where the prevalence of HBV and HCV in the African and Western Pacific regions is higher than in other regions [3,4]. In China, persons with HBV or HCV make up 29.0% and 10.0% of all HBV and HCV cases globally [5]. Most people newly infected with HBV and HCV are often undiagnosed because the infection remains asymptomatic until decades after the infection, when severe symptoms develop with an increased risk of liver damage. Early diagnosis can help prevent the health problems associated with delayed diagnosis and onward transmission. The WHO recommends routine HBV and HCV testing for specific high-risk groups (including migrants from endemic regions) [1,2].

An international migrant is an individual who moves away from their usual country of residence, temporarily or permanently, for various reasons (excluding short-term travel and business trips across an international border) [6]. China’s Reform and Opening-up Policy has attracted many international migrants to live there. Over 846,000 registered international migrants lived in China by 2020, of whom 49.5% resided in Guangdong province [7]. About 95.0% of international migrants came from Asia, Africa, and Latin America, mostly from LMICs, including Vietnam, Brazil, and the Philippines [8]. Globally, international migrants bear a disproportionate burden of viral hepatitis, with migrant children and pregnant women being more vulnerable to infection risk [9]. Meta-analysis estimated that the pooled HBV surface antigen and antihepatitis B prevalence among international migrants were 4.4% (95% CI 3.4%‐5.5%) and 35.2% (95% CI 26.9%‐44.0%), respectively [10,11], and the pooled prevalence of HCV antibody (anti-HCV) and RNA (HCV-RNA) were 1.5% (95% CI 1.1%‐2.0%) and 0.6% (95% CI 0.4%‐0.9%), respectively [11]. Despite the high risk, various systemic barriers persist as global deterrents to health care use among international migrants. Among documented factors, language barriers significantly hinder HBV and HCV testing among migrants, limiting the capacity of health providers to offer testing and the willingness of migrants to accept testing. Additionally, institutional and technical factors, as well as religious issues, have been found to deter the use of health services among international migrants [12].

Findings from previous studies in China show that international migrants are generally young (average age 18‐49 years old), predominantly male, have a higher proportion of high-risk sexual behaviors, and are at an increased risk of hepatitis infection [12]. Factors like language and communication barriers, lack of knowledge of testing venues, lack of medical insurance, and low acculturation remain persistent barriers to the active uptake of HIV and STD testing services [13,14]. These factors also contribute to the reported low use of local medical services among international migrants in China [15]. Therefore, effective intervention measures are urgently needed to promote hepatitis testing uptake among international migrants in China to reduce the health burden and transmission rates [16]. These challenges have contributed to limited policy and financial support for health care promotion among international migrants, discouraging their complete integration into the local community in China and affecting their active engagement in these health care programs.

Pay-it-forward (PIF) is a social innovation strategy that has been proven effective in promoting health services uptake across various populations [17-19] and is based on the theories of upstream reciprocity and mutual aid [20-23]. In the PIF strategy, individuals receive a free test donated by others and are offered the opportunity to voluntarily donate to support another person anonymously [24]. Previous research in China has demonstrated that the PIF strategy can significantly increase STI testing uptake among high-risk populations, largely by leveraging active community engagement and peer-to-peer mobilization. Among men who have sex with men (MSM), gonorrhea or chlamydia and HBV or HCV testing rates are rising from 18.0% to 56.0% and 25.3% to 59.4%, respectively [17,19]. The PIF strategy also increased gonorrhea and chlamydia testing uptake from 4.0% to 82.0% among female sex workers in China [25]. Besides that, PIF has been successfully applied to promote vaccine uptake among vulnerable groups, such as older adults, children, and catch-up age girls [26,27]. Although these findings highlight the potential of PIF, its feasibility and effectiveness remain unexplored among international migrants in China, who face linguistic and cultural barriers and limited community mobilization for health initiatives. Thus, this research aims to evaluate the effectiveness of PIF in increasing HBV and HCV testing uptake among international migrants from LMICs in China using a cluster randomized trial.

## Methods

### Study Design

We will conduct a 2-arm, cluster randomized controlled trial (RCT) to evaluate the effectiveness and acceptability of a PIF intervention to increase HBV and HCV testing uptake compared with standard-of-care among international migrants from LMICs in China. Eligible participants who provide informed consent and complete the baseline survey will be assigned in a 1:1 ratio to one of the 2 study arms: PIF (intervention) or standard of care (control). Using a cluster-randomized design, each cluster of approximately 2–5 participants, defined as a group of patients that arrive together, will be randomly assigned to one of the 2 arms.

The cluster randomized design was selected for the following reasons: (1) to reduce the potential bias due to between-group contamination among participants who arrived with acquaintances or partners; (2) previous researchers found that participants are significantly more likely to receive HIV testing and donate for others when accompanied by a partner than when being alone; hence, the cluster randomized design can promote HBV and HCV test uptake and donation by peer influence; and (3) the cluster randomized design would simplify project management and improve adherence to intervention protocols more than an individual-based randomization [17,19]. We hypothesize that the PIF strategy will be superior to the control (standard medical services in the clinic) in increasing HBV and HCV testing among international migrants from LMICs in Guangzhou.

### Study Settings

This study will be conducted in Guangzhou, the capital of Guangdong province, China. Guangzhou is the primary trading destination for most international migrants in Southern China seeking greener pastures [28]. The interventions will be integrated into the standard procedures of a public hospital located in Sanyuanli, where the largest international migrant community from LMICs operates in Guangzhou [29]. This hospital was selected because it is dedicated and equipped to provide comprehensive health care services to the international population and is well patronized by the migrant community. The clinic is run by an experienced general medical practitioner who has engaged in health promotion among international migrants for over 10 years.

### Participant Recruitment

International migrants visiting the facility will be introduced to the study, and those who express interest will be screened for eligibility. After receiving the primary medical services for their visit, patients will receive co-created health education materials on HBV and HCV that provide basic information about HBV and HCV transmission routes, prevalence in China and among international migrants, prevention, and treatment. All educational materials to be used in the trial were co-designed by a co-creation group consisting of volunteer international students (n=4), an international migrant worker here for business (n=1), an international research fellow working in the field of sexual health in Guangzhou (n=1), a clinician from the international health clinic (n=1), and research staff (MX and AM; n=2). Eligible individuals willing to participate will be required to provide informed consent and complete the baseline survey.

Individuals who migrated to China from an LMIC, aged 18 years and older, have lived in China for at least one consecutive month, have not tested for HBV or HCV in the past 6 months, and were willing to provide informed consent will be eligible for inclusion in the study. Exclusion criteria include a self-reported previous chronic HBV and HCV diagnosis, unwillingness to provide informed consent, and inability to communicate in English, French, or Chinese.

Eligible individuals who provide informed consent will be redirected to the Wenjuanxing platform (Ranxing) to complete a self-administered survey. This baseline survey will collect data on participants’ demographic characteristics, sexual behaviors while in China, history of medical service use in China, and their knowledge of HBV and HCV before participation in the study.

### Randomization and Allocation

Clusters in this study are defined as small groups of participants who arrive at the clinic together or register within the same visit period and may therefore share information that could influence testing decisions. This definition is based on field observations that most international migrants arrive at the clinic alone or with a small number of companions (not more than 2 companions). Therefore, grouping all participants who arrive together into one cluster ensures the feasibility and validity of randomization with a minimum sample size. The decision to group eligible participants who arrive together into a cluster was based on field knowledge that most international migrants arrive at the clinic alone or with not more than 2 companions. Therefore, grouping all participants who arrive together into one cluster ensures the feasibility and validity of randomization with a minimum sample size. Once a cluster is formed, the entire cluster is randomized to either the PIF or control arm, following the pregenerated cluster randomization sequence created by an independent data analyst using SAS (version 9.4; SAS Institute). The allocation sequence will be implemented sequentially as clusters are enrolled. Only the independent data analysts will be blinded, as participants can determine their allocation based on the materials they receive.

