### Sample Size

In a pretest study conducted from April 1 to May 27, 2024, among 20 international migrants from LMICs in Guangzhou, we observed a 90% (9/10) HBV and HCV test uptake rate in the PIF arm and 0% (0/10) in the control arm. However, we adopted the anticipated test rate from another study that applied the PIF strategy to promote HBV and HCV testing among MSM in China (59.4% in the intervention arm and 25.3% in the control arm) to ensure a stable result. Accordingly, we anticipated that 59.4% of participants would accept the dual HBV and HCV testing in the intervention arm and 25.3% of patients would accept testing in the control arm. Based on a 2-sided *t* test (unpooled), an intracluster correlation of 0.10, and an alpha of .05, an anticipated 10 clusters (consisting of approximately 5 participants per cluster) are needed in each intervention arm for the study to achieve an 80% power, resulting in a total sample size of 100 participants.

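### The randomised cluster is described in four ways that do not agree, so the stated 10 clusters per arm and the clustering unit of the primary GEE are not fixed

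*Protocol article*

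**What the plan says.** The protocol article describes the randomised unit in four places.

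- **Abstract, Methods:** participants are "enrolled in blocks of 5 using a cluster randomization plan".
- **Study Design:** "each cluster of approximately 2–5 participants, defined as a group of patients that arrive together", with the whole group assigned to one arm.
- **Randomization and Allocation:** clusters are "small groups of participants who arrive at the clinic together or register within the same visit period". The basis given is that "most international migrants arrive at the clinic alone or with a small number of companions (not more than 2 companions"). The section then says twice that everyone arriving together forms one cluster.
- **Sample Size:** "10 clusters (consisting of approximately 5 participants per cluster") per arm, giving 100 participants in total.

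The sample-size inputs are uptake of "59.4% in the intervention arm and 25.3% in the control arm", a two-sided unpooled t test, an intracluster correlation (ICC) of 0.10 and alpha of .05. Data Analysis specifies a logit-link GEE for the primary outcome that allows for clustering, without naming the unit. Results reports that recruitment ran from September 2, 2024 to February 12, 2025, that 100 people were enrolled, and that uptake and effectiveness will be published separately.

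**The concern.** Arrival groups that mostly number 1 to 3 do not produce clusters of about 5. A cluster of 2 to 5 people arriving together also leaves no place for someone who comes alone, although the article says that this is common. The same-visit-period wording could bridge the gap by pooling several small parties. But no length is given for the period, and no rule says how parties or solo arrivals are combined or when a cluster is full.

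Two things depend on the answer. The first is the sample-size statement, because 10 clusters per arm describes the design only if fives were randomised. The second is the primary analysis. The robust variance of a GEE protects type I error when the model clusters on the unit that was randomised. Study Design points an analyst towards arrival groups, while the Abstract and Sample Size point towards fives. The planned sensitivity analyses vary the correlation structure, not the grouping variable, so they would not reveal a wrong choice of unit.

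**Working it through.** **Inputs (Sample Size).** p1 = 0.594, p2 = 0.253, difference 0.341, ICC 0.10, two-sided alpha 0.05, unpooled t test. K is clusters per arm and m is cluster size.

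**Formula.** Variance of the difference = [p1(1−p1) + p2(1−p2)] × [1 + (m−1) × 0.10] / (K × m). Power comes from the noncentral t distribution with 2(K−1) degrees of freedom.

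p1(1−p1) + p2(1−p2) = 0.2412 + 0.1890 = 0.4302.

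**Step 1: the plan's own figure.** With m = 5 the design effect is 1 + 4 × 0.10 = 1.40.
- K = 10: variance 0.4302 × 1.40 / 50 = 0.01204, SE 0.1097, noncentrality 0.341 / 0.1097 = 3.11, power 83.6%.
- K = 9: power 79.0%.

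Ten is the smallest K that reaches 80%, so 10 clusters per arm and N = 100 reproduce for clusters of 5.

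**Step 2: other cluster sizes at N = 100, ICC 0.10.**

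| Cluster size | Clusters in total | Design effect | Power |
|---|---|---|---|
| 1 | 100 | 1.00 | 95.4% |
| 2 | 50 | 1.10 | 93.0% |
| 3 | 34 (17 per arm) | 1.20 | 90.8% |
| 5 | 20 | 1.40 | 83.6% |

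100 / 3 = 33.3, so groups of at most 3 form at least 34 clusters. Seventeen threes per arm is 51 people; at exactly 50 per arm, power is 90.2%. A few larger parties would lower the count somewhat, since the article says only that most groups are this small.

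**Step 3: clusters per arm needed for 80% power.** 31 at size 1, 17 at size 2, 13 at size 3 and 10 at size 5. The stated 10 is therefore specific to fives.

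**Step 4: clustering on the wrong unit.** I simulated 40,000 trials with no effect: 10 blocks of 5 per arm, beta-binomial outcomes with ICC 0.10, and uptake of 25.3% in both arms. The model was a logit GEE with independence working correlation and robust variance. As an assumption, each block was made up of arrival groups of 2, 2 and 1. The correction multiplies the variance by K/(K−1) and uses t with 2(K−1) degrees of freedom, where K is the number of analysis clusters per arm (10 or 30).

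| GEE clustered on | No correction | Small-sample correction |
|---|---|---|
| Block of 5 (the randomised unit) | 7.1% | 4.2% |
| Arrival groups 2+2+1 | 8.6% | 7.4% |

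Without correction, 7.1 − 5.0 = 2.1 points of excess arise even with the right unit, because 20 clusters are few for an uncorrected robust variance. The wrong unit adds 8.6 − 7.1 = 1.5 points. With the correction, which brings the right unit below 5%, the wrong unit adds 7.4 − 4.2 = 3.2 points.

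**The case against.** The strongest reply is that the texts can be partly reconciled. The same-visit-period limb allows small parties and solo arrivals to be combined into clusters of about 5, and the size statements are hedged as approximate or as describing most patients. The sample-size arithmetic is sound for fives, and the cluster variable is normally named in an analysis plan, which is not shown. All of that stands. But the article never states a pooling rule, and Study Design defines the cluster by arrival together alone. The conflict lies between the article's own statements, so it is not merely detail left to another document.

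A reader might draw four stronger conclusions, which the document does not support.

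- **The trial is underpowered.** At N = 100 and ICC 0.10, power exceeds 80% at every cluster size in the table, and smaller clusters raise it. Power would fall (34% at size 1, 69% at size 3) only if recruitment had stopped at 10 small clusters per arm, but 100 people were enrolled.
- **Unblinded staff could select patients into a known arm.** Randomization and Allocation has the cluster formed first and then randomised from a sequence pregenerated by an independent analyst. Study Design assigns people after consent and the baseline survey. Staff who know the current arm do not necessarily know the next one.
- **Pooling defeats the contamination rationale.** Pooling whole parties keeps companions in the same arm, and the article expects people in the same visit period to share information.
- **The 50/50 split in Table 2 shows that fives were randomised.** It is compatible with fives but does not establish them.

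**Conclusion.** The point holds as an inconsistency in the definition of the randomised unit. The stated cluster count is right for clusters of about 5. It is wrong if arrival groups of 1 to 3 were randomised, when there would be about 34 to 100 clusters and power of about 91% to 95%. The consequence for inference is conditional: no passage says that the GEE will cluster on a unit other than the one randomised. If fives were randomised and arrival groups used in the model, type I error would rise to about 7% to 9%, and only part of that would be due to the wrong unit.

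These figures rest on the stated ICC of 0.10, equal cluster sizes within each scenario and the assumed 2+2+1 make-up of a block. The matter can still be settled, since the article reports only part of the descriptive analysis as complete.

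**What to change.** 1. Adopt one definition throughout: a cluster is the set of participants assigned by one entry of the randomisation list. Reconcile the Abstract, Study Design, Randomization and Allocation, and Sample Size to it.
2. Say how people arriving alone were placed and what a visit period was. Recruitment is over, so report how membership was actually fixed; a new enrolment rule can no longer be imposed.
3. Carry the list-entry ID into the analysis file and name it as the GEE cluster variable. If there are only about 20 clusters, specify a small-sample variance correction with a t reference distribution.
4. Report the realised number and size distribution of clusters by arm, and restate the cluster count and power for that unit.

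The cost is wording and one variable in the analysis file. The stated cluster count may change, and the confidence interval for the primary comparison may become slightly wider.

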### Intervention

Participants randomly assigned to the intervention arm will receive the PIF intervention. In the PIF arm, participants will receive counseling on HBV and HCV infection risks and the need for routine testing and HBV vaccination. They will then watch a 2-minute video (Multimedia Appendix 1) and receive a printed infographic card (Multimedia Appendix 2) introducing the PIF concept. The video and infographic card were drafted by the research team based on PIF research experiences among MSM and female sex workers and submitted to the co-creation group for review. The video introduced HBV and HCV, the risk of infection among international migrants, and the concept of the PIF strategy. The infographic card showed the four steps of PIF and provided the research WeChat (Tencent Holdings Ltd) QR code and a telephone number to facilitate participation. Only the revised versions of all materials approved by the co-creation group were used in the study.

Participants will be informed that they are eligible for a free HBV and HCV test, funded by donations from a previous participant. Testing will be voluntary, and participants consenting to testing will provide blood samples. Regardless of the testing decision, all participants will be offered the opportunity to make monetary donations of any amount to support testing for subsequent participants. Participants will be reminded that testing and donation choices are voluntary, and accepting or declining either or both will not disqualify them from the study. Donations can be made online by scanning the Alipay (Ant Group Co Ltd) or WeChat QR code provided or offline by depositing cash into the official PIF donation box placed in the physicians’ office.

Control arm participants will only receive the same educational materials on HBV and HCV, but no PIF-related information. They will be informed that they are eligible for HBV and HCV testing at an out-of-pocket cost of US $5.91 (43 RMB), as the test is not covered under insurance. Participants will be reminded that testing is voluntary and that they may decline without repercussions. Those who accept and pay the cost will be directed to provide blood samples for testing.

All tests in the study will be conducted using the HBV surface antigen test (Guangzhou Wondfo Biotech Co., Ltd) and the anti-HCV test (Guangzhou Wondfo Biotech Co., Ltd), which are approved for use in China and, at the time of this writing, used at the study site. Depending on their preferences, tested participants can receive their test results in person 2 hours after the sample provision or online via the phone number they provided as part of the hospital’s standard registration process. Those who test positive will be offered treatment services at the facility at their own cost. All participants in arms will also receive an informational card detailing the names, locations, working hours, and price lists of HBV vaccination centers near the study site.

